## 8. Data collection and analysis

### 8.1 Data collection

The medical records of patients will be inputted directly into the computer system, which is securely stored in the facilities where the evaluation will take place. To facilitate the exchange of data for further analysis among researchers, an Excel spreadsheet will be sent, containing only the unique identification number of each patient. This approach ensures the confidentiality and security of the data.

### 8.2 Statistical analysis

#### 8.2.1 Baseline characteristics

To check whether outcome and demographic baseline measures will be balanced among intervention groups, comparisons will be conducted using analyses of variance (ANOVA) or chi-square tests (i.e., SCS group and EX+SCS group) to analyze significant differences between groups (p>0.05)

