## 4. Sample size

The sample size will be estimated using GPower® software (Franz Faul, Universität Kiel, Kiel, Germany), version 3.1.9.2. As there are no similar studies allowing for the calculation of sample size based on reference means and standard deviations, a comparison will be made using the difference between two dependent means of 1.95 normal populations, assuming equal standard deviations of 3,2 according to the results obtained from a prior study [37]. Thus, the calculation will be based on the primary outcome of "Disability" and will consider an effect size of 0.70, a power of 0.95 for ANOVA repeated measures, and an alpha error of 0.05. A total of 40 participants (20 subjects per group) will be included in this study. Moreover, considering the probability of loss during follow-up (30%), 12 more participants considering dropout (6 participants per group) will be included, resulting in a total of 52 participants. The possibility of increasing the number of subjects will be explored in case of insufficient statistical power to reach these predefined levels. In the event of dropouts, noncompliance, or absence of results, an intention-to-treat analysis will be conducted.

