#### 8.2.2 Analysis of the outcome measures

Following the Consolidated Standards of Reporting Trials (CONSORT) guidelines on the reporting of RCTs, a per-protocol analysis will be performed. The normality assumption will be checked with the Kolmogorov–Smirnov test and box-plot analysis, while the homogeneity of the variance will be tested through the Levene test. To analyze the acute and short-term effects of SCS and SCS combined with core and control motor exercise on PSPS T2, a two-way ANOVA for repeated measures with experimental groups (i.e., Post3weeks, Post2months, Post6months) as factors will be used, followed by Tukey corrections, to examine time, group, and interaction effects through within- and between-group comparisons (primary and secondary outcomes). The results will be presented as the mean difference (MD) and confidence interval at 95% (IC95%). Effect size (ES) will be estimated by calculating Cohen’s d coefficient. All analyses will be performed using the statistical analysis software SPSS 24 (IBM Inc., Chicago, Illinois, USA). In the case of dropouts during the study or if the statistical power is less than the established 80%, an intention-to-treat principle analysis will be performed [71]. The normality of the data will be tested by visual inspection of histograms, and the characteristics of the participants will be presented using descriptive statistical tests. To assess between-group differences in response to treatment at each post-baseline time point, the mean between-group differences and their associated 95% confidence intervals (CI) will be calculated by constructing mixed linear models using interaction terms (group vs. time). The treatment effects will be adjusted by including baseline outcome values as covariates in the model. Statistical analysis will be conducted by a researcher who is not involved in any of the phases of data collection and will receive data in coded form. Minimal clinically important differences are patient-derived scores that reflect changes in a clinical intervention that are meaningful to the patient. To do this from the delta percentage (Δ%) will calculate using the standard formula: change (%) = [(post-test score − pre-test score)/pre-test score] × 100.

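### Baseline balance is checked with significance tests at a reversed or ambiguous threshold, and the plan does not say that the ODI conclusion rests on the baseline-adjusted model

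*Protocol article*

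**What the plan says.** Section 8.2.1 gives the purpose and the tool: "To check whether outcome and demographic baseline measures will be balanced among intervention groups, comparisons will be conducted using analyses of variance (ANOVA) or chi-square". The criterion is worded as "to analyze significant differences between groups (p>0.05".

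Section 8.2.2 then describes two analyses. The first is a two-way repeated-measures ANOVA for the primary and secondary outcomes. It lists the 3-week, 2-month and 6-month assessments and names no baseline covariate. The second is a set of mixed linear models with a group-by-time interaction, giving between-arm differences at each follow-up time. The sentence after it reads: "The treatment effects will be adjusted by including baseline outcome values as covariates in the model". That adjustment does not depend on the tests in 8.2.1. Section 8.2.2 does not say which of the two analyses decides the result for the Oswestry Disability Index (ODI), the primary outcome.

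The arm sizes come from section 4: "A total of 40 participants (20 subjects per group) will be included in this study", and for dropout "12 more participants considering dropout (6 participants per group) will be included, resulting in a total of 52 participants". That is 20 per arm, or 26 per arm as recruited.

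**The concern.** Three things look wrong.

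- The threshold. Significance is normally p below 0.05. As printed, p above 0.05 is attached to significant differences. It may have been meant loosely as the criterion for balance, but the text does not say so.
- The method. In a properly randomised trial the null hypothesis of a baseline test is true by design, so a rejection is a chance event. Non-rejection does not show that the realised difference is small. What matters is whether the realised difference in a prognostic variable shifts the treatment comparison, and adjustment answers that where a p-value cannot.
- The consequence. The mixed model is protected by its baseline covariate. The repeated-measures ANOVA, as described, is not. If the ODI conclusion were drawn from the ANOVA, precision would be lost and a chance baseline imbalance would carry into the estimate.

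**Working it through.** **Inputs.** 20 and 26 per arm (section 4). Two-sided 0.05, because the two-arm ANOVA F test equals a two-sided t test. Baseline-to-follow-up correlation ρ = 0.5 or 0.7, which is an assumption because the protocol gives none. The plan states no imbalance limit, so there is no figure of its own to reproduce here; the arm sizes follow as 40/2 = 20 and 52/2 = 26.

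**1. Largest observed difference that is still non-significant (continuous variable).** d = t(0.975, 2n−2) × √(2/n).
- n = 26: 2.009 × √(2/26) = 0.557 SD.
- n = 20: 2.024 × √(2/20) = 0.640 SD.

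For a binary variable near 50% with symmetric splits, the first uncorrected chi-square result below 0.05 is 17/26 v 9/26 (31 percentage points) or 14/20 v 6/20 (40 points).

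**2. Bias in an unadjusted comparison, given an imbalance.** Bias = ρ × observed baseline difference. For 0.5 SD: 0.5 × 0.5 = 0.25 SD and 0.7 × 0.5 = 0.35 SD. With 26 per arm, t = 0.5 × √(26/2) = 1.80 and p is about 0.08, so the test would not flag it. In simulation with the imbalance fixed at 0.5 SD and no treatment effect, the unadjusted rejection rate is about 11–16% (26 per arm) or 9–11% (20 per arm). With baseline adjustment it is about 5%.

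**3. How often that happens.** With the difference measured in population SDs (standard error √(2/n)), a chance imbalance of at least 0.5 SD in a given variable arises in about 7% of trials at 26 per arm and 11% at 20. One that large which also passes the test arises in about 2.4% and 6.5%.

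**4. Type I error over all trials.** Simulating randomised trials with no treatment effect and an unadjusted follow-up comparison gives about 5% overall, and 3.4–4.5% among trials whose baseline test was non-significant. There is no inflation.

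**5. Precision.** The ratio of adjusted to unadjusted standard error is approximately √(1−ρ²).
- ρ = 0.5: √0.75 = 0.87.
- ρ = 0.7: √0.51 = 0.71.

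In variance terms the adjusted analysis removes 25% or 49%.

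**The case against.** The strongest reply is that nothing turns on these tests. Section 8.2.1 only checks. No covariate, model or conclusion is made to depend on the outcome, and the mixed model adjusts for the baseline outcome unconditionally. Unadjusted comparisons are in any case protected by randomisation, on average over trials. All of this stands, and it means that deleting the tests would by itself change no result.

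A reader might infer more from the section than it supports:
- *That passing the balance test raises the false-positive rate.* It does not. The rates of 9–16% hold only given an observed imbalance of about 0.5 SD; over all trials the rate is about 5%, and lower among those that pass.
- *That the test often misses true baseline differences.* Its power against a true 0.5 SD difference is indeed only 42% (26 per arm) or 34% (20 per arm), but under randomisation no true difference exists, so these figures describe nothing in this trial.
- *That the test selects covariates.* The protocol says nothing of the kind.
- *That about 95% of comparisons would be labelled different.* This is the literal reading of the threshold, but p above 0.05 can also be read as the criterion for balance. The fair charge is that the wording is reversed or ambiguous.

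The reply does not close the gap in 8.2.2. The adjustment sentence refers to the model and follows the mixed model; the ANOVA for the same outcomes is described without it, and no priority is stated.

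**Conclusion.** The point holds in a limited form. The baseline tests give no useful information and their threshold needs correcting, but that is a minor matter of wording. The part worth acting on is that an ANOVA described without baseline adjustment stands beside a baseline-adjusted mixed model for the same outcomes, with the ODI conclusion assigned to neither.

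If the unadjusted result were used, the cost would be a standard error larger by a factor of about 1/0.87 = 1.15 to 1/0.71 = 1.41. In the minority of trials with a chance baseline ODI imbalance of about 0.5 SD, there would also be a bias of 0.25–0.35 SD. Both ranges rest on the assumed correlations of 0.5 and 0.7. They also take the ANOVA as printed, with only post-baseline times and no covariate.

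**What to change.** In 8.2.1, delete the ANOVA and chi-square balance tests and the bracketed p-value threshold. Describe baseline characteristics by arm as mean (SD) or n (%).

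In 8.2.2, state that the between-arm conclusion for ODI and the other outcomes rests on the baseline-adjusted mixed model whatever imbalance is observed, and that no unadjusted between-arm ANOVA result is used for the conclusion.

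This needs no extra patients, visits or data. The only loss is the p-value column in the baseline table.

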#### 8.2.2 Analysis of the outcome measures

Following the Consolidated Standards of Reporting Trials (CONSORT) guidelines on the reporting of RCTs, a per-protocol analysis will be performed. The normality assumption will be checked with the Kolmogorov–Smirnov test and box-plot analysis, while the homogeneity of the variance will be tested through the Levene test. To analyze the acute and short-term effects of SCS and SCS combined with core and control motor exercise on PSPS T2, a two-way ANOVA for repeated measures with experimental groups (i.e., Post3weeks, Post2months, Post6months) as factors will be used, followed by Tukey corrections, to examine time, group, and interaction effects through within- and between-group comparisons (primary and secondary outcomes). The results will be presented as the mean difference (MD) and confidence interval at 95% (IC95%). Effect size (ES) will be estimated by calculating Cohen’s d coefficient. All analyses will be performed using the statistical analysis software SPSS 24 (IBM Inc., Chicago, Illinois, USA). In the case of dropouts during the study or if the statistical power is less than the established 80%, an intention-to-treat principle analysis will be performed [71]. The normality of the data will be tested by visual inspection of histograms, and the characteristics of the participants will be presented using descriptive statistical tests. To assess between-group differences in response to treatment at each post-baseline time point, the mean between-group differences and their associated 95% confidence intervals (CI) will be calculated by constructing mixed linear models using interaction terms (group vs. time). The treatment effects will be adjusted by including baseline outcome values as covariates in the model. Statistical analysis will be conducted by a researcher who is not involved in any of the phases of data collection and will receive data in coded form. Minimal clinically important differences are patient-derived scores that reflect changes in a clinical intervention that are meaningful to the patient. To do this from the delta percentage (Δ%) will calculate using the standard formula: change (%) = [(post-test score − pre-test score)/pre-test score] × 100.

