## 6. Program feasibility and safety: Attendance and compliance

There are numerous obstacles and factors that affect the adherence to exercise for individuals with chronic lower back pain [67]. Patients with spine pain are increasingly seeking personalized exercise programs [68]. However, studies have shown that home-based interventions supported by individualized video-based exercise programs result in greater improvement following treatment [69]. The proposed intervention in this study combines these two perspectives. During the initial phases, individualized training will be provided to ensure compliance with the treatment plan and minimize potential complications. Additionally, once the patient begins working from home, the exercises will be accompanied by videos to facilitate daily monitoring of the intervention. Moreover, WHO defines adherence as “the extent to which a person’s behaviour—taking medication, following a diet, and/or executing lifestyle changes—corresponds with the agreed recommendations from a healthcare provider". In the therapeutic exercise group, participants will be encouraged to follow the guidelines at home to complement the intervention. The exercise group should perform the therapeutic exercises according to the instructed regularity as per the SIRAS scale [70].

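### Per-protocol is the named analysis of a superiority trial, intention-to-treat is conditional under two conflicting rules, and neither rule says which is primary

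*Protocol article*

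**What the plan says.** Section 8.2.2 (Analysis of the outcome measures) opens with the analysis set: "Following the Consolidated Standards of Reporting Trials (CONSORT) guidelines on the reporting of RCTs, a per-protocol analysis will be performed". Further on, the same section makes an exception for "dropouts during the study or if the statistical power is less than the established 80%, an intention-to-treat principle analysis will be performed". The per-protocol set is not defined, and nothing says how or when power is to be assessed.

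Section 4 (Sample size) has its own rule: "In the event of dropouts, noncompliance, or absence of results, an intention-to-treat analysis will be conducted". It plans the trial with "a power of 0.95 for ANOVA repeated measures, and an alpha error of 0.05", and adds: "The possibility of increasing the number of subjects will be explored in case of insufficient statistical power to reach these predefined levels".

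Section 6 (Program feasibility and safety) sets an adherence expectation for one arm: "The exercise group should perform the therapeutic exercises according to the instructed regularity as per the SIRAS scale". The end of Section 1 makes clear that the aim is superiority, since the combined treatment is expected to do better than either treatment alone.

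**The concern.** In a superiority trial the primary comparison should keep patients in the groups to which they were randomised. Section 8.2.2 starts from the opposite default. It justifies this by a guideline that the same sentence describes as being about reporting, which is no reason to choose one analysis set over another.

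The two sections also disagree on when ITT applies, and neither ranks the two analyses when both exist. Two answers to the main question, on disability measured by the Oswestry index (ODI), could then be on the table with no prior rule for choosing between them. If the per-protocol set excludes non-adherent exercisers, it compares a selected exercise group with a control group that faces no matching selection.

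**Working it through.** **1. The two rules side by side**

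| Situation | Section 8.2.2 | Section 4 |
|---|---|---|
| Dropouts | ITT | ITT |
| Noncompliance without dropout | Per-protocol stands | ITT |
| Absence of results | Not mentioned | ITT |
| Power below target | ITT if below 80% | No ITT condition; a larger sample is explored |
| Stated power | 80% | 0.95 |
| Which is primary if both are run | Not stated | Not stated |

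The second row is a direct contradiction about the same patients: Section 4 sends noncompliers to ITT, whereas per-protocol would normally remove them. The 80% called established in Section 8.2.2 matches nothing in Section 4.

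**2. Will the dropout condition be met?** Section 4 plans 40 patients plus 30%: 40 + 0.30 × 40 = 52. If losses are independent with probability 0.30, P(no dropout among 52) = 0.70^52 ≈ 9 × 10⁻⁹. Even at 5% loss it is 0.95^52 ≈ 0.07. ITT will almost surely be run, so the open question is its status.

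**3. What the power condition amounts to.** Assume that power is computed from the observed effect in a two-group t-test with 20 per arm (38 degrees of freedom, two-sided alpha 0.05).
- The critical t is 2.024, and a noncentrality of 2.875 gives 80% power.
- Observed power therefore reaches 80% only if |t| ≥ 2.875, that is, p ≤ 0.0066. At p = 0.05 observed power is about 50%.
- The condition restates the p-value. With no effect it is met in about 99% of trials (1 − 0.0066).
- If true power were the planned 0.95 (noncentrality 3.70), P(|t| < 2.875) ≈ 21%.

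**4. What per-protocol could do.** This is an illustration; these assumptions are not in the document: no true effect, 26 per arm, normal outcome at one time point, the least adherent 30% or so of the exercise arm excluded and no controls, adherence correlated r with good outcome.
- Keeping the top 70% of a standard normal adherence score gives a retained mean of φ(−0.524)/0.70 = 0.3477/0.70 ≈ 0.497.
- The bias is r × 0.497 SD.
- Error rates are from simulations of 20,000 to 40,000 trials per setting.

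| r | Bias (SD) | ITT type I error | Per-protocol type I error | Success claimed on either set |
|---|---|---|---|---|
| 0 | 0.00 | about 5% | about 5% | about 7% |
| 0.2 | 0.10 | about 5% | about 6% | about 8% |
| 0.3 | 0.15 | about 5% | 7% to 8% | about 10% |
| 0.5 | 0.25 | about 5% | about 13% | about 15% |

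**5. Two contrasts.** If ITT strictly replaces per-protocol unless per-protocol reaches about p < 0.006, type I error is about 5% to 6% over the same range of r. If both arms lose the same share by the same mechanism, per-protocol type I error is also about 5% to 6%.

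**The case against.** The strongest reply is that ITT will be run anyway. The conditions in Section 8.2.2 are joined by 'or', dropout is a matter of trial conduct and not of results, and Section 4 separately promises ITT for noncompliance. This stands, and it limits the point. A reader might infer that the analysis set depends on the result. The documents do not support that as a description of what will happen: the dropout condition will almost surely settle the matter first, and the text speaks only of statistical power, without saying that it is observed power. Even if the power rule did operate, it would be met in only about 21% of trials at the planned 95% power, and literal switching gives about 5% to 6% type I error. The 8% to 15% figures need success to be claimed on whichever set is significant. The plan does not state this; it only fails to exclude it.

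A reader might also infer that per-protocol favours exercise. Section 6 says how exercisers should behave; it is not an exclusion rule, and no per-protocol set is defined. Section 4 divides its dropout allowance equally, six per group. The direction is plausible, but it is an inference.

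Finally, the sample-size increase in Section 4 might be read as using the same trigger. It does not: it refers to that section's own levels, with power of 0.95, and describes no test at 40 followed by a retest.

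It could also be said that an article leaves such detail to an analysis plan. That does not help here, because the article does state the rule, twice and inconsistently.

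**Conclusion.** The point holds in this form. Per-protocol is the named analysis of a superiority trial, ITT is conditional, Sections 4 and 8.2.2 conflict on the conditions and on the power level (0.95 against 80%), and neither fixes which result is primary. This follows from the text alone and needs no simulation. Because ITT will almost surely exist beside per-protocol, the practical defect is a choice left open after the data are seen.

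The size is conditional. Per-protocol bias of about 0.10 to 0.25 SD and type I error of about 6% to 13% require exclusions confined to the exercise arm, at about 30%, with adherence–outcome correlation of 0.2 to 0.5. With exclusions unrelated to outcome there is no bias, although having two sets to choose from still gives about 7%. The reading of the power condition as a restated p-value holds only if power is computed from the observed effect. The point should be corrected before analysis, since it decides which disability result is the trial's headline.

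**What to change.** Change the wording in Sections 4 and 8.2.2 so that both say the same:

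- The primary analysis is ITT, unconditionally: all randomised patients in their allocated arm, all available visits, in the baseline-adjusted mixed model with group-by-time terms that Section 8.2.2 already plans.
- Per-protocol is a sensitivity analysis, with the set defined in advance, including what adherence means in each arm.
- The power condition for ITT and the attribution to CONSORT are deleted.
- The 80% and 0.95 figures are aligned.

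As a separate and secondary matter, delete the open-ended sample-size increase in Section 4, or limit it to one blinded look at the pooled ODI standard deviation.

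The cost is wording only. The ITT estimate may be somewhat smaller than the per-protocol one, and the freedom to enlarge the trial ad hoc is given up.

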#### 8.2.3 Correlation coefficient

The strength of the relationship between the variables will be examined using the Pearson correlation coefficient and/or Spearman correlation coefficient (for non-compliance with the normality assumption).

## 9. Dissemination plan

The dissemination of research findings is an essential component of the research process, and this study places considerable emphasis on various aspects of it. The results of this study will be published in scientific journals that are focused on the fields of medicine, physiotherapy, and exercise. By being published, the study will be shared with the broader scientific community, ensuring that the knowledge gained from the research is accessible to professionals and researchers in these fields. Moreover, all members of the research team are highly skilled in the areas of exercise and spinal cord stimulation, and they are also experienced researchers in their respective fields. This allows them to make valuable contributions to the development of articles during the future publication process. Additionally, the protocols implemented for the treatments will be described in detail to enhance transparency and increase the reproducibility of the study’s results. It is important to note that the study’s results may be provided to third parties if there is a justifiable cause and it is accepted by the authors.

